#### Statistical analysis

The outcome data will be analysed once at the end of the trial follow-up period (ie, no interim analyses of accumulating outcome data will be undertaken), with participants being analysed as part of the group to which they were assigned. We will compare the average cotinine levels between the groups using a linear multilevel model controlling for pertinent baseline covariates (at the child and school level), minimisation factors and adjusting for clustering by schools. The distributional assumptions will be checked and different link functions (eg, log link) will be used if indicated. Checks for data quality and completion rates will be carried out on a regular basis.

### Economic evaluation

We will undertake a full cost-effectiveness analysis using methods that have already been piloted.^5^ The first stage estimates the training cost and the cost of delivering the intervention. We will use a service-use questionnaire developed from the questionnaire used in the pilot to record the utilisation of healthcare resources. The self-administered questionnaire will be completed by students. We, therefore, will not ask for details regarding, or limit our questions to, specific diagnoses or settings. We will also record and calculate the costs of medications related to these illnesses, which are dispensed. Quantities of resource use (contacts) are multiplied by local unit costs to derive an individual cost profile for each participant.

We will measure health-related quality of life in children by using the EQ-5D-Y,^9^ which will be administered at baseline and each follow-up period. The results will be used to calculate quality-adjusted life years (QALYs) for children in the trial, using the area under the curve. In addition, the symptoms for lower respiratory infection and otitis media collected in the symptom diary will be used to estimate DALY changes for all children in the trial.

We will conduct an incremental cost-effectiveness analysis of SFI over and above the control. Costs and QALYs will be combined to calculate the incremental cost-effectiveness ratio in terms of incremental cost per QALY gained.

### Process evaluation

A mixed-methods process evaluation will explore three key functions: mechanisms of action, context and implementation.^19^

Mechanisms of action (mediators and acceptability): all children (in the intervention and control arms) will complete a short questionnaire at the 3-month and 6-month follow-ups, measuring mechanisms of action constructs as mediators of behaviour change (see table 2). These are based on the evidence for the links between the behaviour change techniques^20^ that constitute the active ingredients of the intervention, and the respective mechanisms of actions^21^ of those techniques (see table 2 and figure 1).

**Table 2 T2:** The logic model of the SFI

Resources	Activities	Outputs (for process)	Short term outcomes	Medium term outcomes	Long term outcomes	Impact
Year-5 schoolteachers’s relevant resource materials; teacher training; teachers training to pick up any signs of distress among children as an untoward consequence of SFI; 2×45 m sessions over 2 consecutive days	Storytelling, drama and role-play activities focused on building children’s confidence in raising their concerns about SHS with their parents/carers and enhancing their negotiation skills, and allowed children to learn and practise relevant negotiating strategies. 1. Information about health consequences 2. Salience of consequences 3. Behavioural practice/rehearsal 4. Goal setting (behaviour)	Evidence of practising strategies, developing skills and confidence around SHS negotiation; evidence of knowledge of harms	Smoke-free homes (SFH)/SHS negotiation self-efficacy; SFH/SHS negotiation intentions; evidence of knowledge of harms; knowledge; Mechanisms of Actions (MOA); intentions; skills; beliefs about consequences; knowledge	Self-reported smoking restrictions; salivary cotinine; AE monitoring: distress arising from smoking-related illness (SRI)	Frequency severity of respiratory symptoms; lung function tests	APQ; school absenteeism; quality of life (EQ-5D-Y); health service use
Four refresher sessions (15 min each) over the subsequent 4 weeks	The discussion, quiz and games aimed to make children aware of the harms of SHS and motivate them to achieve a smoke-free home. Revising the salient points of the initial sessions, encouraging children to share their experience of initiating relevant conversations within their families encouraging children to share their experience of initiating relevant conversations within their families. 1. Information about health consequences 2. Salience of consequences 3. Behavioural practice/rehearsal 4. Goal setting (behaviour)	Evidence of knowledge of harms of SHS from quiz answers; evidence of motivation to achieve SFH from games; evidence of sharing relevant experiences of initiating conversations around SHS and SFH	SHS risk awareness, SHS negative outcome expectancies; SFH intentions; SFH/SHS negotiation self-efficacy; SFH/SHS negotiation intentions; MOA; knowledge; beliefs about consequences; intentions			
Home promise forms for families (described in activities)	Reading of graphic representations of the hazards of SHS, pictorial guidance to help them make their homes smoke free and a tear-off slip to commit to imposing smoking restrictions at home visitors and cars. 1. Goal setting (behaviour) 2. Problem solving 3. Action planning 4. Behavioural contract	Evidence that the home promise form was taken home	Action planning to negotiate SFH/SFH self-efficacy; SFH intention; MOA; intentions; beliefs about consequences; behavioural regulation; behavioural cueing			

APQ, Academic Performance Questionnaire; SFI, smoke-free intervention; SHS, secondhand smoke; SRI, smoking-related illness.

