### Outcomes assessments

A causal link between SHS exposure and respiratory infections is well established.^3^ In the form of salivary cotinine, we also have a highly sensitive and specific biomarker of SHS exposure.^18^ Therefore, we propose SHS exposure (proximal) and respiratory symptoms (distal) as the primary and secondary outcomes, respectively. The outcomes for this definitive trial will be measured before and after the intervention in each of the study’s arms (see table 1 for the schedule of assessments).

**Table 1 T1:** Schedule of assessments within the CLASS III trial

Assessments	Baseline	Post-intervention		
		Month 3	Month 6	Month 12
Eligibility and consent	X			
Sociodemographic and medical history				
Personal details	X			
Household details	X			
Medical conditions and history of medications	X			
Smoking-related behaviours				
Smoking restrictions and social visibility	X	X	X	X
Attitudes toward smoking	X	X	X	X
Health service use	X	X	X	X
Quality of life	X	X	X	X
Exposure to SHS—salivary cotinine	X	X		
Respiratory symptoms diary		X	X	X
Academic assessment				
APQ	X	X	X	X
School absenteeism report	X	X	X	X
AE reporting		X	X	X
Process evaluation		X	X	

AE, adverse event; APQ, Academic Performance Questionnaire; CLASS III, Children Learning About Secondhand Smoke; SHS, secondhand smoke.

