### Primary outcome

We intend to use children’s salivary cotinine as a biomarker of SHS exposure at baseline and month 3. Cotinine—the major proximate metabolite of nicotine—has a relatively long half-life (17 hours), which allows detection of tobacco exposure even after 3 days.^18^ Once children are enrolled in the study, saliva samples will be obtained from all participating children at baseline and again at 3 months post-randomisation. Samples can be stored at ambient temperature for a period of 2 weeks before transported to a specialist laboratory—ABS Labs (https://www.abslabs.co.uk/) in the UK—these are to be analysed using a gas–liquid chromatography technique. Samples will not contain any participant-identifiable information and will only have the trial enrolment number.

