### Data collection methods

Prior to randomisation, a baseline assessment will include a classroom-administered questionnaire (including EQ-5D-Y,^9^ health service use and smoking behaviour) to be completed by participating children, Academic Performance Questionnaire (APQ) and school absenteeism form completed by schoolteachers and saliva sample collection by the research team for each child. Each child will also receive a respiratory symptoms diary with instructions on how to use it. Follow-up assessment will take place at 3 months, 6 months and 12 months post-randomisation from all eligible and consenting participants. All assessments carried out at the baseline will be repeated at the follow-up assessment except cotinine levels, which will only be assessed at month 3 post-randomisation.

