Fidelity to delivering the six SFI sessions will be assessed using a fidelity index, linked to the behaviour change techniques^27^ that underpin the SFI. A third of intervention schools (six in each country) will be randomly selected and their six SFI sessions will be observed by two independent checkers using the fidelity index.

We will also interview 2–3 policy-makers in each country to explore their views on opportunities for implementing and scaling up the SFI and how best to work with schools and policy-makers to overcome the obstacles and maximise the opportunities.

All FGDs and interviews will be conducted face-to-face using a topic guide to ensure consistency, with ﬂexibility to allow participants to generate naturalistic data on what they see as important. Prior to commencing data collection with teachers and parents, we will collect consent (this will have been previously secured for headteachers and children). In these discussions, we will use a hermeneutics approach,^28^ which encourages participants to discuss features of the intervention to elicit data on their experience of its delivery/receipt. With the participants’ permission, the FGDs and interviews will be audio-recorded digitally and transcribed verbatim.

The quantitative acceptability questionnaire and fidelity data will be analysed descriptively. Mediator analysis will test the proposed causal model. Verbatim transcripts, of FGD and interview data, translated into English, will be analysed using the framework approach, whereby data are organised into matrices (for headteachers, class teachers, students and parents). Integration of the datasets will be done using a ‘triangulation protocol’.^29^

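### For month-3 cotinine, the mediator schedule cannot establish that the mediator came before the exposure, so the promise to test the causal model is too strong for that step

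*Protocol article*

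**What the plan says.** All statements are in the protocol article.

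- **Mediators** (Process evaluation): children in both arms "will complete a short questionnaire at the 3-month and 6-month follow-ups, measuring mechanisms of action constructs as mediators of behaviour change". Table 1 agrees: its row reads "Process evaluation X X", with no mark at baseline.
- **Cotinine** (Primary outcome): "saliva samples will be obtained from all participating children at baseline and again at 3 months post-randomisation". Data collection methods confirms that baseline assessments are repeated at follow-up "except cotinine levels, which will only be assessed at month 3 post-randomisation".
- **What cotinine reflects** (Primary outcome): it "has a relatively long half-life (17 hours), which allows detection of tobacco exposure even after 3 days".
- **Assumed order** (Table 2, logic model): knowledge, beliefs, skills and intentions are short-term outcomes. The medium-term column that follows begins "Self-reported smoking restrictions; salivary cotinine; AE monitoring".
- **Claim** (Process evaluation): "Mediator analysis will test the proposed causal model".

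Contextual factors, by contrast, are measured at baseline as well as at months 3 and 6. Table 1 also lists attitudes toward smoking, and smoking restrictions with social visibility, at baseline and every follow-up. The protocol does not name either as a mediator scale.

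**The concern.** A test of a causal chain needs data that could contradict its direction. Here the chain runs from what the child knows, believes and intends, through negotiation at home, to lower exposure. Cotinine describes exposure over roughly the last three days before the month-3 visit, and the mediator questionnaire is completed at that visit. If the home became smoke-free during the weeks of delivery, the child may report more self-efficacy, stronger intention or more habit because the negotiation worked. Without a baseline mediator score, a child who was already confident, in a family already inclined to restrict smoking, also looks like a case of mediation.

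Mechanisms of action are a stated objective, and so is learning how to scale up. An indirect effect on cotinine presented as a tested mechanism could point later programmes to the wrong component.

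**Working it through.** **Timing.** Lag from mediator measurement to the follow-up cotinine sample:

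| Mediator wave | Cotinine sample | Lag |
|---|---|---|
| Month 3 | Month 3 | 3 − 3 = 0 months |
| Month 6 | Month 3 | 3 − 6 = −3 months |

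No wave has a positive lag. For smoking restrictions and respiratory symptoms, which are also collected at months 6 and 12, month-3 mediators lead by 3 and 9 months.

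**Size of a false indirect effect.** The protocol gives no figure for mediation, so there is none to reproduce. Its one usable anchor is the target difference under Sample size: 0.28/1.38 = 0.203, taken as a total effect of 0.2 SD. The remaining inputs are assumptions: a direct effect of teaching on the mediator of 0.5 SD and residual variances of 1. Effects are scored so that benefit is positive. The indirect effect is a × b, where a is the effect of allocation on the mediator and b is the slope of outcome on mediator given allocation. There is no true mediation in cases 1 and 2.

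*1. Reverse influence of size r (outcome changes mediator).* a = 0.5 + 0.2r and b = r/(1 + r²).

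| r | a × b | Share of 0.2 |
|---|---|---|
| 0.05 | 0.51 × 0.05/1.0025 = 0.0254 | 13% |
| 0.10 | 0.52 × 0.10/1.01 = 0.0515 | 26% |
| 0.20 | 0.54 × 0.20/1.04 = 0.1038 | 52% |
| 0.30 | 0.56 × 0.30/1.09 = 0.1541 | 77% |

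*2. Shared background factor with loadings l (mediator) and k (outcome).* a = 0.5 and b = lk/(1 + l²).

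| l, k | a × b | Share of 0.2 |
|---|---|---|
| 0.2, 0.1 | 0.5 × 0.02/1.04 = 0.0096 | 5% |
| 0.3, 0.2 | 0.5 × 0.06/1.09 = 0.0275 | 14% |
| 0.5, 0.3 | 0.5 × 0.15/1.25 = 0.0600 | 30% |

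**Can the planned data tell the cases apart?** A simulation with 68 schools of 34 children, 500 runs, assumed effects and a total effect of about −0.20 gave mean indirect effects of −0.198 under true mediation, −0.199 under pure reverse influence and −0.144 under a shared cause alone. All were significant in every run, using ordinary standard errors without a clustering correction.

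**What each remedy does.** Take the strongest shared factor above (0.5, 0.3).

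- *Ordering alone:* a later outcome with the same loading gives the same b, so the false share stays at 30%.
- *Adjusting for a baseline mediator:* the factor's variance falls to 1 − 0.25/1.25 = 0.8, so b = 0.12/1.20 = 0.10 and the share is 0.5 × 0.10/0.2 = 25%. The modest gain reflects the low implied correlation between baseline and follow-up mediator, 0.25/1.25 = 0.20.
- *Adjusting a later outcome for its baseline and month-3 values:* the variance falls to 1/(1 + 0.09 + 0.09) = 0.847, so b = 0.127/1.212 = 0.105 and the share is about 26%.

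That last adjustment has a price. Suppose mediation is complete and realised by month 3 (0.5 × 0.4 = 0.20), and residual outcome stability is ρ. Conditioning on the month-3 outcome then leaves 0.20 × (1 − ρ), which is 0.10 at ρ = 0.5 and 0.04 at ρ = 0.8 (both values assumed).

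**The case against.** The protocol speaks of mediators of behaviour change, not of cotinine alone. Smoking restrictions are a medium-term outcome in Table 2 and are measured after month 3, so ordered tests are already possible. The choice of wave, outcome, lag and covariates normally belongs in the analysis plan, which is not shown, as Figure 1 is not. The process evaluation is framed as exploratory and includes focus groups, interviews and triangulation. Baseline cotinine, attitudes and restrictions offer some control of pre-existing differences. Reverse influence is also less obvious for knowledge of harms than for self-efficacy.

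Most of this stands, and it limits the point. A reader might infer that the trial cannot test its causal model at all, or that it will announce which mechanism produced the effect. The documents support neither. The effect of allocation on month-3 mediators is testable, later outcomes can be analysed in order, and the stated aim is to explore mechanisms. A reader might also infer that ordering in time is the main cure. It helps against reverse influence but leaves stable confounding where it was.

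The cotinine step is not answered. The measurement times are fixed in the protocol, cotinine sits downstream of the mediators in the logic model, and the claim to test that model makes no exception for it. An analysis plan can choose a model, but it cannot supply an earlier measurement.

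**Conclusion.** The point holds for the step from mediator to month-3 cotinine. On the stated schedule, an indirect effect on cotinine is a concurrent association. It has a causal reading only if month-3 scores stand for earlier levels and there is neither reverse influence nor unmeasured confounding.

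The false share is about 13% to 77% for reverse effects of 0.05 to 0.30 SD and about 5% to 30% for the shared factors considered. These ranges illustrate the problem under the assumptions above. They are not estimates for this trial, and the upper ends should not be read as the expected bias.

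The primary effectiveness comparison and the sample size are unaffected. The change is worth making because it alters what the trial may conclude about mechanism.

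**What to change.** 1. **Wording (Process evaluation).** State that mediation of month-3 cotinine will be reported as a concurrent, exploratory association, adjusted for baseline cotinine and for the baseline attitude and smoking-restriction items already collected, with sensitivity analyses for reverse causation and unmeasured confounding. The cost is text and a modest amount of analysis.
2. **Baseline mediators.** Where baseline is still open, add the short mediator scales to the classroom baseline questionnaire and adjust for them. The cost is a few minutes per child. The gain depends on how strongly baseline and follow-up scores correlate. Schools already past baseline would lack these scores.
3. **Ordered tests.** Use month-3 mediators with month-6 and month-12 smoking restrictions and respiratory symptoms, adjusting for baseline values where they exist (Table 1 shows no baseline symptom diary). Keep adjustment for the month-3 outcome as a sensitivity analysis only, since it can remove mediation already realised by then. These data are already planned. Stable confounding remains and should be stated as a limitation.

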#### Smoke-free intervention

All participating children in the intervention arm will receive the SFI delivered by their teachers. Teachers will receive prior training in delivering the intervention. This training will focus on addressing their knowledge gaps around tobacco, improving skills in using a variety of teaching methods and their ability to build confidence within and teach negotiation skills to children.

The intervention will consist of:

Two 45-minute sessions delivered over 2 days by schoolteachers. The duration of these sessions has been planned to fit within a regular school lesson. These sessions will consist of a flip chart presentation and a drama activity, respectively. The session activities are specially designed to increase pupils’ knowledge about SHS and related harms and to negotiate smoke-free homes with their parents/carers who will implement smoking restriction rules. The seven acts of the drama, to which parents/carers are invited to attend, will give children the opportunity to practise their negotiating skills and be confident within their cultural context. It will also serve as a visual incentive for the parents/carers not to smoke inside homes.Children will be given an achievement certificate to record the seven achievements to make their homes smoke free. Children will also receive a promise form that describes the main step to achieve a smoke-free home, that is, to walk seven steps away from the house door to smoke. It will also contain a tear-off slip to make a commitment to impose smoking restrictions at home. Children will take promise forms to their parents/carers, show them the messages and negotiate with them to ‘sign-up’ to the smoke-free homes ‘promise’ form.A set of 4 follow-up sessions (15 min each) to reinforce key messages delivered in the initial sessions to be delivered once a week over 6–7 weeks after the 2 initial sessions. The immediate first follow-up session will be based on feedback from parents/carers about the drama activity. The second and third follow-up sessions will consist of a word search game and a quiz game in which children will be asked questions and given answer options. The final follow-up session will be based on small group discussions among the students about their experiences of negotiating smoke-free homes and if they faced any challenges.

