### Usual education

Schools in the control arm will receive the SFI at the completion of the trial.

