### AEs procedures

We are expecting a minimal number of adverse events (AEs) and no serious adverse events (SAEs) during the study. SFI is an educational intervention and has been very well received in our previous studies^16 30^ without leading to any directly related AEs. Nevertheless, there will be a vigilant surveillance system in place for AEs occurring during the course of the trial with particular emphasis on identifying, recording, reporting and managing any SAEs. We will sensitise school teachers to look for signs of any AEs resulting from the interactions between children and their parents/carers. We will also encourage children and parents/carers to report any related adversities.

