#### Detecting, recording and reporting of AEs and SAEs

In the event of any AE reported by the child, their parents/carers, schoolteachers, and research assistants will complete an AE form, which will include a medical diagnosis, if relevant and available. The research assistant will also call the trial manager on the same day providing a verbal report of the event. The trial manager will ensure that the event is classified appropriately after receiving the verbal report. All AEs will be reported to the principal investigators (Bangladesh and Pakistan) within 3 days of detection. AE data will be collated and reported to the trial sponsors and National Bioethics Committee at 6 monthly intervals, and also be reported to the Study Operational Committee and the Independent Trial Steering Committee (ITSC) at their regular meeting. All SAEs must be reported to the principal investigator within 24 hours of detection and should also be reported to the trial sponsors and National Bioethics Committee within three working days. All serious events must also be reported to all study investigators and the chair of the ITSC within 3 days. The Chief Investigator will have the overall responsibility to ensure that all AEs are reported according to the above protocol.

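### Training teachers to notice child distress is listed as part of the SFI, and families are prompted only for related events, so adverse events may be detected more often in the SFI arm

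*Protocol article*

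**What the plan says.** Some of the protocol article's text on adverse events is specific to the SFI or to perceived cause, and some is general.

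**Specific to the SFI or to perceived cause**
- Process evaluation, Table 2, resources column: "teachers training to pick up any signs of distress among children as an untoward consequence of SFI".
- Smoke-free intervention: "Teachers will receive prior training in delivering the intervention".
- Usual education: "Schools in the control arm will receive the SFI at the completion of the trial".
- AEs procedures, on teachers: "We will sensitise school teachers to look for signs of any AEs resulting from the interactions between children and their parents/carers".
- AEs procedures, on families: "We will also encourage children and parents/carers to report any related adversities".

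**General**
- AEs procedures: "there will be a vigilant surveillance system in place for AEs occurring during the course of the trial".
- The subsection on detecting and recording events, on what triggers a form: "In the event of any AE reported by the child, their parents/carers, schoolteachers, and research assistants will complete an AE form".
- Outcomes assessments, Table 1: AE reporting is marked at months 3, 6 and 12, with no distinction by arm.

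The section on cluster randomisation and allocation states that neither children nor teachers can be masked. Both groups are sources of AE reports. No section says whether AE training and prompting are the same in the two arms.

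**The concern.** The SFI asks children of about 9 to 12 years to negotiate smoking rules with adults at home. Distress or family conflict is the harm one would look for, and the protocol itself anticipates it. Such events also occur without the SFI, and the control arm is the only source for that background rate. It can serve this purpose only if events are looked for in the same way in both arms.

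Two features of the text work against that. First, training to notice distress appears as an ingredient of the SFI and is framed as spotting a consequence of the SFI, so a site that follows Table 2 would train intervention teachers only. Second, the prompt to families is for related events. A control family has received nothing to which an event could be related, and so has little reason to respond.

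An excess of events in the SFI arm could then be partly or wholly a product of detection, and a real excess could be dismissed for the same reason. A low total could also reflect reporters screening out events that they judged unrelated.

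**Working it through.** **Is there a plan figure to reproduce?** No. The document states no AE rate, no AE power and no between-arm AE analysis. Its sample size calculation concerns salivary cotinine and has no bearing here. The check is therefore a comparison of the text, followed by an illustration on assumed values.

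**Step 1. Compare the channels by arm, as written.**

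| Channel | Section | SFI arm | Control arm during follow-up |
|---|---|---|---|
| Teacher training to notice distress | Table 2, SFI resources | Yes | Not as an SFI resource, since the SFI comes after the trial |
| Teacher sensitisation to events from child-parent interactions | AEs procedures | Yes | Not excluded; arm not stated |
| Prompt to children and parents | AEs procedures | Related events | Related events, but nothing to relate them to |
| General surveillance | AEs procedures | Yes | Yes |
| AE reporting at months 3, 6 and 12 | Table 1 | Yes | Yes |
| Form for any reported AE | Detecting, recording and reporting | Yes | Yes |

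The last three rows are common to both arms. The first row differs by arm, and the third has the same wording but cannot work in the same way in both. The AE form comes into play only once someone has reported an event, so it does not correct a difference in who is trained or prompted to report.

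**Step 2. Extra contact in the SFI arm.** The Smoke-free intervention section ends its follow-up sessions with group discussion of children's experience of negotiating at home. The Process evaluation section places focus groups with children and parents in 12 intervention schools, and observers at all six sessions in a third of intervention schools. These are further occasions on which family conflict may come to light, and control schools do not have them.

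**Step 3. The target event.** It is described in three ways: distress caused by the SFI (Table 2, resources), distress arising from smoking-related illness (Table 2, medium-term outcomes), and events arising from child-parent interactions (AEs procedures). These need reconciling whatever is decided about the arms.

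**Step 4. How unequal detection carries through.** Let the true risk be p in both arms, and the detection probabilities s_I (SFI) and s_C (control).

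Observed risk ratio = (p × s_I) / (p × s_C) = s_I / s_C

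All detection values below are assumed:
- 50% v 40%: 0.50/0.40 = 1.25
- 60% v 45%: 0.60/0.45 = 1.33
- 60% v 30%: 0.60/0.30 = 2.0
- 60% v 20%: 0.60/0.20 = 3.0
- equal detection, however incomplete: 1.0

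Neither p nor the sample size appears in the result, so more children do not reduce the bias.

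**Step 5. What this could look like in this trial.** Children per arm: 34 schools × 40 = 1360. Assume p = 2% in both arms and detection of 60% v 30%.

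- Expected recorded events: 1360 × 0.02 × 0.60 = 16.3 and 1360 × 0.02 × 0.30 = 8.2.
- Observed risks: q_I = 0.012, q_C = 0.006. Chance of a nominally significant difference ≈ Φ(|q_I − q_C|/SE − 1.96), with SE² = [q_I(1 − q_I) + q_C(1 − q_C)]/n.
- Ignoring clustering (n = 1360): SE = 0.00362, 0.006/0.00362 = 1.66, giving about 38%.
- Borrowing the cotinine design effect of 2.98 (n = 1360/2.98 = 456): SE = 0.00625, 0.006/0.00625 = 0.96, giving about 16%.

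Over assumed risks of 1% to 5% and detection ratios of 1.33 to 3, that chance runs from 8% to 96% ignoring clustering, and from 5% to 58% with the borrowed design effect. A range this wide shows that the document does not fix the size.

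**The case against.** The strongest reply is that the operative AE text is the AE section, not one cell of a logic model. That section describes surveillance throughout the trial and sensitises teachers without naming an arm. The target of that sensitisation is events from child-parent interactions, which happen in control homes too. Table 1 sets one AE schedule for everyone, and a form follows any reported event. Table 2 lists the distress training separately from teacher training, and the Smoke-free intervention section does not mention distress when it sets out what SFI training covers. AEs are not among the listed outcomes and no AE comparison is specified; the described use is oversight. Quality of life, health service use and absenteeism are collected on the same schedule in both arms and could show some harm. Extra vigilance in intervention schools is also a reasonable safeguard.

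Much of this stands. A reader might infer that AE detection is tied altogether to SFI training and to related events, so that ascertainment must differ and the trial could not show whether the SFI causes harm. The documents do not support that reading: surveillance, schedule and form are open to both arms and to any event, and teacher sensitisation is not restricted by arm. Nor is the lack of a stated AE analysis in an article a fault.

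The narrower point survives. Table 2 still counts distress training as an SFI resource, the prompt to families is still limited to related events, and nothing says that these are equalised across arms. The common questionnaire outcomes are not specific to distress or family conflict. Vigilance can be kept and given to both arms.

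**Conclusion.** The point holds in limited form. As written, the SFI arm has one detection channel that control schools lack during follow-up, and solicited reports from families are filtered by perceived cause. With unmasked reporters, adverse events may be recorded more often in the SFI arm, and anyone who sets the counts side by side would face possible detection bias. The likely direction is towards more events in the SFI arm.

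The size cannot be estimated from the document. The ratios of 1.25 to 3.0 and the counts of about 16 v 8 are illustrations on assumed risks and detection probabilities; the significance figures also depend on a design effect borrowed from cotinine. The conclusion rests on reading Table 2 as a description of what intervention schools receive, and it would fall away if the full protocol states that AE training and prompting are identical in both arms. The change is worth making because it replaces stated wording with a less biased procedure at little cost.

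**What to change.** In AEs procedures:
1. Give the same short AE briefing and the same AE form to year-5 teachers in all 68 schools at the baseline visit, before allocation. The briefing should cover recognising and reporting events, without SFI content.
2. Replace the prompt for related adversities with a question about any adverse event, asked in the same way of children and parents in both arms at months 3, 6 and 12.
3. Record relatedness afterwards, as a separate field, and not as a condition for reporting.

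In Process evaluation, Table 2: reconcile the table with AEs procedures by listing distress detection as a trial procedure in both arms instead of an SFI resource, and use one description of the target event throughout.

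Cost: a brief addition to a baseline assessment that already takes place in every school, and one question at follow-ups where AE reporting is already scheduled. The small downside is that more unrelated events will be recorded and must be classified.
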